## Abstract

**Introduction:** Relapse is very common in drug abusers and contributes to a series of negative consequences. Effective addiction treatment exists but there are some problems in the implementation process. Mobile health (mHealth) offers a potential solution to improving recovery outcome for drug abusers in the community. The research team developed a community-based addiction rehabilitation electronic system (CAREs). The primary aim of this study is to explore whether the integrated rehabilitation based on program CAREs promotes drug abusers to keep abstinence. The secondary aim is to evaluate the impact of CAREs on interaction between drug users and service providers, and on addiction-related physical and social functions.

**Method and analysis:** A randomized controlled trial (RCT) will be conducted. The study is a superiority trial with parallel group design. Seventy drug abusers who are newly ordered to undergo community rehabilitation will be recruited from the community in Shanghai. Participants will be 1:1 randomly assigned to receive integrated community rehabilitation by using CAREs or only receiving routine community rehabilitation for 6 months. Corresponding social workers will provide service and monitor their drug use behavior in accordance with the routine work-flow. Outcomes will be assessed at baseline and in the 6th month. The primary outcome is the performance on illicit drug urine test which will be carried out regularly twice per week during the study period. Secondary study outcomes include longest duration of sustained abstinence, days that participants interact with social workers, and the decrease rate of addiction-related issues severity index. Chi-square tests and ANOVAs will be used to compare characteristics of the members of the two groups. GEE will be used to compare the seven dimensions scores of the ASI between groups.

**Discussion:** The study provides evidence for the feasibility and effectiveness of the “CAREs” system through comparing the results of the intervention group with the control group. This paper describes the design and methodology of the study.

**Ethics and dissemination:** The Ethical Board of SMHC approved the study protocol. All participants will present for the informed consent process. After study completion, the results will be published.

**Trial Registration:** ClinicalTrials.gov NCT03451344, https://clinicaltrials.gov/ct2/show/NCT03451344

## Introduction

Drug abuse is a global public health problem (1). In recent years, the number of individuals who use drugs in China has increased year by year. By the end of 2017, the total number of individuals who use drugs in China has been 2.505 million (2), but the actual number of drug users is much higher than that. In order to control China's increasingly serious drug epidemic phenomenon and related hazards, since the promulgation of the “Anti-drug Law” in 2007, China has established a trinity addiction treatment model with three forms: isolated compulsory treatment, voluntary treatment provided by qualified medical institutions, and treatment of drug addiction in the community (community-based rehabilitation) (3, 4).

Among them, the community-based rehabilitation has become one of the most important measures to treat drug addiction (5). Community-based rehabilitation refers to the efforts of community uniting families, public health and safety agencies, civil affairs departments, and other social resources to help drug abusers to achieve long-term abstinence. Community-based rehabilitation also helps drug abusers to restore physical and mental health, enjoy equal opportunities, and become free from social discrimination. The number of new reported community addiction was 245,000 and the number of community rehabilitation was 59,000 in China in 2016 (2). However, due to the lack of relevant interventions, around 40–60% drug abusers who were ordered to undergo the community-based rehabilitation relapsed, or were incarcerated, were referred to compulsory treatment, or died (6). Therefore, it is a pressing issue to help drug abusers to improve their anti-relapse skills and increase the detoxification rate in the community.

At present, China's community drug treatment and community rehabilitation are still at an initial stage of development and are still immature (7). There are some difficulties and challenges that cannot be ignored. They are mainly manifested in the following aspects: (1) due to limited funding, the community public facilities are inadequate; (2) community workers find it difficult to provide professional and systematic services because of their lack of professional consciousness and professional competence; (3) there is a serious shortage of community staff and a high turnover rate (8). In addition, according to the Anti-drug Law of the People's Republic of China, community drug treatment lasts 3 years, which is a long time for both drug abusers and social workers (3, 7). This brings a further challenge to the community drug treatment and community rehabilitation. Therefore, it is imperative to explore new ways for community drug treatment and community rehabilitation.

Mobile health (mHealth) is a term used for the practice of medicine and public health supported by mobile communication technology (such as PDA, mobile phones, and satellite communications). mHealth applications include the use of mobile devices in collecting community and clinical health data, delivery of healthcare information to practitioners, researchers, and patients, real-time monitoring of patients' vital signs, and direct provision of care. With the popularity of smartphones, the spread of smartphone technologies opens up doors for mHealth projects, particularly for chronic disease management. Since an APP named “WellDoc” approved by the U.S. FDA for the prevention and treatment of diabetes (9), the United States FDA has approved more than 31 mobile health products by 2015. In practice, the main functions of mobile health services include disease and health information, education, disease screening, assessment and monitoring, intervention, and patient self-management, and social support (10). In the study field of drug treatment and rehabilitation, international exploration is conducted through the Internet (11), mobile phone SMS (12, 13) and APPs (14), which offers professional intervention to persons with substance use disorders. At present, the ecological momentary assessment (EMA) is mainly used. The advantage of this technology is to collect real-time data and immediately evaluate and intervene on high-risk factors of patients to prevent relapse (15, 16). The data shows that it has certain effects on providing knowledge of drug addiction and coping skills for high-risk situations for relapse and reducing relapse rates. For cocaine users, using EMA technology to dynamically monitor the relapse factors such as the location and emotional changes of individuals with substance use disorders can significantly improve their self-detection and management capabilities and help them stop using drugs (17). For HIV prevention the participants were sent weekly relevant prevention information in the form of text messages. After 6 months, the results showed that the intervention group had a lower risk of HIV infection than the control group (18). In recent years, the development of mobile health researches has become a hot topic in China, but there is lack of relevant researches in the field of drug addiction.

In 2003, a new model of community-based drug treatment and rehabilitation “Dominated by the Government, Self-operated by the Community and Involved by Society” emerged in Shanghai (19). More than 800 professional social workers in the addiction recovery services are currently providing community services for around 70,000 drug abusers who were ordered to undergo community-based rehabilitation. Although Shanghai has a pioneering attempt in China's community drug treatment and rehabilitation, community service providers and resources remain severely inadequate. There is an urgent need for new means of intervention and technology to improve the efficiency and effectiveness of community drug treatment and rehabilitation. The good news is that China's mobile phone popularity rate has improved significantly and the use of mobile phone APPs has become people's daily behavior (20). Due to the current situation, community-based rehabilitation program in Shanghai exploring the mutual integration of a mHealth rehabilitation model based on the mobile APP is a good opportunity.

The research team developed a community-based addiction rehabilitation electronic system (CAREs) based on a smartphone app, including the functions of education, support, and psychological interventions. CAREs is an electronic information platform for both community drug users and service providers. The goal of the system is to address the social psychological support needs of the persons with substance use disorders in the community, to improve the professionalization and standardization of community rehabilitation, and to further improve the efficiency of community-based drug rehabilitation, and ultimately help the drug users in the community to stay abstinent. In this study, the investigators will use the method of quantitative research to evaluate the effectiveness of using the electronic management system of drug rehabilitation in clinical work. This study is of important social significance to improve the community drug addiction / rehabilitation model in Shanghai and provide important theoretical basis for the future research in the field of substance abuse treatment.

This paper outlines the protocol for a randomized controlled trial (RCT) of the community-based addiction rehabilitation electronic system (CAREs) based on a smartphone application. This interactive system consists of an APP for clients and a webpage for service providers, with the aim of teaching clients craving and emergency coping skills and helping service providers to improve their work efficiency in communities. The primary aim of this study is to explore whether the integrated rehabilitation based on CAREs promotes drug abusers to stay abstinent. The investigators hypothesize that the integrated rehabilitation group will show significant improvement in performance on illicit drug urine tests. The secondary aim is to evaluate the impact of CAREs on the interaction between drug users and service providers, and on addiction-related physical and social functions.

## Methods and analysis

### Trial design

This is a randomized controlled trial (RCT). The study uses parallel group design and is a superiority trial to explore whether the integrated rehabilitation based on CAREs promotes drug abusers to stay abstinent. The study divides participants into integrated and standardized community-based rehabilitation groups in a ratio of 1:1 and has 2 arms: the participants in integrated rehabilitation group will receive regular community-based rehabilitation plus CAREs with their matched social workers, the participants randomized to the standardized community-based rehabilitation group will only receive routine community-based rehabilitation.

### Study setting

The setting for this study is in Shanghai, China. According to the Anti-Drug Law which was issued in 2007, drug abusers discharged from compulsory treatment programs should receive community-based rehabilitation for around 2 years. In Shanghai, community social workers in the addiction recovery services are employed by the government to help drug users and monitor their drug use behavior. There are around 1,000 social workers serving about 70,000 drug users in Shanghai.

### Eligibility criteria

Drug abusers who are newly ordered to undergo community-based rehabilitation will be recruited for the study. Candidates are eligible to participate if they are aged 20–50 years, meeting the DSM-5 (Diagnostic and Statistical Manual of Mental Disorders-V) criteria for substance dependence, and are willing to comply with the relevant requirements of the study including using the mobile app. People who are unable to use mobile phones or have a history of suicidality or a significant cognitive impairment will not be recruited. There is no limitation for gender when recruiting participants.

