### Outcomes

The primary outcome is the performance on urine drug screen (UDS) which will be carried out regularly during the study period twice per week. The results of urine tests will be examined in the difference of proportion of drug-positive samples between two groups. Urine test kit will be used to test drug use including heroin, amphetamine-type stimulants, marijuana, cocaine, and ketamine. A subject who does not submit urine samples during the intervention period or who refuses to submit a sample even if he/she is present at the site will be considered as having a positive UDS.

Secondary outcomes include: (a) longest duration of sustained abstinence, defined as the longest continuous record weeks of negative urine drug screen samples; (b) interaction with social workers in the addiction recovery services: the days that participants interact with their corresponding social workers will be collected during the study period. Any phone call, SMS, face-to-face meeting, or communication via CAREs will be considered as one interaction; (c) the decrease rate of addiction-related issues severity index: the Chinese translation of the Addiction Severity Index (ASI) that has good reliability and validity in China will be used to assess the severity of addiction at enrollment and 6 months after enrollment. The reliability and validity of the Chinese version of the instrument have been assessed (21, 22). The internal consistency of the seven dimensions was judged to be acceptable (alpha = 0.44~0.79), the test-retest reliability was good (ICC = 0.68~0.84), and the inter-rater reliability was good (ICC = 0.87~0.98). The descent rate will be counted via dividing the minus value between baseline score and 6 months score by baseline score (assessments completed at assessment phases shown in Table 3).

**Table 3 T3:** Assessments completed at assessment phases.

**Assessments**		**Assessment Phase**		
		**T1**	**T2**	**T3**

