### Participant timeline

Individuals who express interest will be invited to participate in informed consent procedures. Those who voluntarily consent to participate will then enter a 3 days screening to determine whether they meet inclusion/exclusion eligibility criteria. Baseline measurements of drug use and UDS will also be collected at this time. Participants who continue to meet eligibility criteria will participate in a 7 days induction period. During the induction period, participants and their corresponding social workers will be trained by technicians to get familiar with CAREs. Participants will be randomly assigned, in a 1:1 ratio, to receive either the intervention program or control program for a period of 6 months. Subsequent assessment points coincide for both groups at 6 months after randomization (see Figure 4).

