### Assignment of interventions

#### Allocation

Those that consent will be randomized using simple randomization tables generated by SPSS Statistics (version 22) (24); 35 subjects will be assigned to the usual group (routine community-based rehabilitation) and 35 to the integrated rehabilitation group (routine community-based rehabilitation + CAREs intervention).

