### Data management

Intention-to-treat principle will be used in the statistical analysis. All statistical analyses will be conducted using SPSS Statistics (version 22) (24). Chi-square tests and ANOVAs will be used to compare characteristics of the members of the two groups. Primary outcome and secondary outcomes (results of urine illicit drug tests between the groups, the days that participants interact with their corresponding social workers) will be compared between groups using analysis of ANOVAs. Considering behavioral clinical trials often find data missing at the end of trials due to incomplete evaluations, Generalized Estimating Equations (GEE) will be used to compare the seven dimensions scores of the ASI between group across the study period. Any unfavorable changes to participants during the study period will be recorded. Since this study does not impact participants' routine care and is examining the effect of an integrated community-based rehabilitation for drug abusers in communities, no serious adverse events are anticipated and no interim analyses are planned.

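### Baseline urine drug screen is collected but has no stated role in allocation or in the primary comparison; adding it as a covariate would protect the result from chance imbalance and gain precision at almost no cost

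*Protocol article*

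**What the plan says.** The points below are all from the protocol article.

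- **Aim (Trial design).** The trial is a superiority trial "to explore whether the integrated rehabilitation based on CAREs promotes drug abusers to stay abstinent".
- **Entry (Eligibility criteria).** Candidates are newly ordered to community-based rehabilitation, aged 20 to 50, willing to comply, and "meeting the DSM-5 (Diagnostic and Statistical Manual of Mental Disorders-V) criteria for substance dependence". No urine result or period of abstinence is required.
- **Source population (Study setting).** By law, "drug abusers discharged from compulsory treatment programs should receive community-based rehabilitation for around 2 years".
- **Baseline (Participant timeline, Table 3).** At screening, "Baseline measurements of drug use and UDS will also be collected at this time".
- **Allocation (Allocation).** Assignment uses "simple randomization tables generated by SPSS Statistics", 35 to each arm, with no stratification named.
- **Primary outcome (Outcomes).** "The results of urine tests will be examined in the difference of proportion of drug-positive samples between two groups". Samples are taken twice a week during the study period.
- **Analysis (Data management).** The urine results and the days of interaction with social workers "will be compared between groups using analysis of ANOVAs". No covariate is named.

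The Addiction Severity Index (ASI) is treated differently. Its decrease rate is divided by the baseline score, and its seven dimensions are analysed by GEE. The urine outcome has no comparable use of its baseline value.

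**The concern.** Whether a person is using at entry is likely to predict the share of positive samples over the next six months. A participant who is still using can give positive samples from the first test. One who has just left compulsory treatment drug-free can give them only after a return to use. Entry admits both.

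With 35 per arm and unstratified allocation, the arms may differ by chance in how many enter positive. An unadjusted ANOVA carries that difference into the estimated effect. The variation explained by baseline status also stays in the error term, so the confidence interval is wider than it needs to be. The trial already holds the measurement that would deal with both.

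**Working it through.** **Inputs.** From the documents: 35 per arm, simple randomisation, ANOVA, two tests a week for six months, a rate of about 40% and a 60% relative reduction (Sample size). The planned difference is therefore 0.60 × 40 = 24 points. The documents give neither the prevalence of a positive baseline UDS nor its prognostic strength, so both are assumed and varied. The 40% under Sample size is not stated to be a baseline urine rate. The plan has no figure of its own on baseline balance to reproduce.

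**Step 1: size of the chance imbalance.** Let m of the 70 participants be positive at baseline and X of these fall in one arm of 35. Then X is hypergeometric, and the between-arm difference is D = (2X − m)/35.

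Var(X) = 35 × (m/70) × (1 − m/70) × (35/69), and SD(D) = 2 × SD(X)/35.

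For m = 28: Var(X) = 35 × 0.4 × 0.6 × 35/69 = 4.26, SD(X) = 2.06, SD(D) = 0.118.

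| Baseline-positive (assumed) | SD of difference | P(difference ≥ 20 points) |
|---|---|---|
| 7/70 (10%) | 7.2 points | 1% |
| 14/70 (20%) | 9.6 points | 3.4% |
| 28/70 (40%) | 11.8 points | 8.7% |
| 35/70 (50%) | 12.0 points | 15.1% |

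Twenty points is 7 participants. When m is even the smallest qualifying gap is 8 (for example 18 against 10), so the probabilities do not rise smoothly with m.

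**Step 2: effect on the primary result.** The expected shift is the imbalance times the gap in positive-sample rate between baseline-positive and baseline-negative participants. Two assumed cases, both averaging 40% when 40% enter positive:

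- Strong predictor, 70% against 20%: a one-SD imbalance shifts the result by 11.8 × 0.50 = 5.9 points, and a 20-point imbalance by 20 × 0.50 = 10 points.
- Weak predictor, 55% against 30%: the shifts are 11.8 × 0.25 = about 3 points and 20 × 0.25 = 5 points.

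**Step 3: simulation.** 4,000 trials, 52 samples per participant (2 × 26 weeks), beta-binomial counts, 40% positive at baseline. ANOVA was compared with ANOVA plus baseline UDS.

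| | Strong: unadjusted | Strong: adjusted | Weak: unadjusted | Weak: adjusted |
|---|---|---|---|---|
| Type I error, all trials | 5.4% | 5.2% | 5.0% | 4.7% |
| Type I error when imbalance ≥ 20 points | 29% | 5% | 12% | 2% |
| SE of effect, no true effect | 0.0839 | 0.0602 | 0.0723 | 0.0666 |
| Power, 30% reduction | 33% | 49% | 41% | 44% |
| Power, 60% reduction | 92% | 99% | 96% | 97% |

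Reduction in SE: 1 − 0.0602/0.0839 = 28% (strong) and 1 − 0.0666/0.0723 = 8% (weak). The power figures depend on the assumed spread between participants and serve only to compare the two analyses. They do not check the planned sample size.

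**The case against.** The strongest reply is that randomisation already handles this. Unadjusted ANOVA is valid, its overall type I error is about 5%, and any small unstratified trial has the same exposure. A covariate could also be named in an analysis plan that is not shown. The first part stands, and it limits the point to precision and to distortion of a single realised result. The second stands only in part. The article does not leave the method open: it names ANOVA for the primary outcome, so the suggestion improves a stated method and does not ask for missing detail.

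Several stronger readings are tempting, but the documents do not support them.

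- **Drug use before the intervention counts as failure.** Only samples taken during the study period count, and Table 3 lists the baseline UDS separately. Earlier use enters only if it continues or is still detectable, and on average equally in both arms.
- **The baseline result is used nowhere.** Data management compares the characteristics of the two groups, which may well include baseline UDS. Such a table would show an imbalance but would not correct for it.
- **The trial mixes two legal tracks, one of them active users.** Table 1 mentions a community-addiction track, but it describes what the app can do. Eligibility criteria names rehabilitation orders, and the two-monthly tests under Interventions match Table 1's rehabilitation schedule, not the monthly one. Many participants may therefore enter drug-free, and a dependence diagnosis does not by itself imply current use.
- **The aim of staying abstinent should be judged in baseline-negative participants only.** If 40% enter positive, that leaves 0.60 × 35 = 21 per arm. For 20% against 8% (the planned 60% reduction), two-sided power on a two-proportion approximation is about 20%. The hypothesis in the Introduction concerns performance on urine tests, which applies to every participant.

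**Conclusion.** The point holds as a modest and concrete improvement. Baseline UDS is collected, but the article gives it no role in allocation or in the primary comparison, and 35 per arm is small enough for this to matter. If 20% to 50% enter positive, an imbalance of at least 20 points has a probability of about 3% to 15%. In the simulated case with 40% positive, the unadjusted false-positive rate given such an imbalance was 12% to 29%, against 2% to 5% with adjustment. Averaged over all randomisations it stays near 5%, so a reader should not infer that the design is biased or that a difference between arms is uninterpretable.

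The gain in SE runs from about 8% to 28%, depending on a prognostic strength that the documents do not give. If nearly everyone enters negative, the gain is small and so is the exposure.

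**What to change.** In Data management, replace the unadjusted ANOVA for the primary outcome with wording such as: *The proportion of drug-positive samples per participant will be compared between arms in a linear model with terms for arm and baseline UDS (positive or negative), in all randomised participants.* Define a positive baseline by the same drug panel as the outcome samples, and state that the term is dropped if no participant is positive at baseline. Use the same two terms for longest sustained abstinence.

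Results by baseline UDS status may be shown descriptively, marked as imprecise. Entry and allocation need not change. Recruitment has already begun, so the model should be fixed before anyone looks at outcomes by arm.

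The cost is a change of wording and one model parameter. The data are already collected, and no further participants, visits or tests are needed.
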